#### Chronic Obstructive Pulmonary Disease and Asthma Cases and Outcomes

As test cases, we will develop and test our approach using (1) COPD, (2) pediatric asthma, and (3) adult asthma. For COPD, we will adjust the criteria used by the Centers for Medicare and Medicaid Services and National Quality Forum [78-80] to incorporate outpatient and emergency room visit data [81] to find COPD patients. A patient is deemed to have COPD if he/she is ≥40 years and has one of the following:

1 outpatient visit diagnosis code of COPD (International Classification of Diseases, Ninth Revision [ICD-9]: 491.21, 491.22, 491.8, 491.9, 492.8, 493.20, 493.21, 493.22, 496; International Classification of Diseases, Tenth Revision [ICD-10]: J41.8, J42, J43.*, J44.*) and ≥1 prescription of tiotropium within 6 months of the outpatient visit.≥2 outpatient or ≥1 emergency room visit diagnosis codes of COPD (ICD-9: 491.21, 491.22, 491.8, 491.9, 492.8, 493.20, 493.21, 493.22, 496; ICD-10: J41.8, J42, J43.*, J44.*).≥1 hospital primary discharge diagnosis code of COPD (ICD-9: 491.21, 491.22, 491.8, 491.9, 492.8, 493.20, 493.21, 493.22, 496; ICD-10: J41.8, J42, J43.*, J44.*).≥1 hospitalization with a primary discharge diagnosis code of respiratory failure (ICD-9: 518.81, 518.82, 518.84, 799.1; ICD-10: J80, J96.0*, J96.2*, J96.9*, R09.2) and a secondary discharge diagnosis code of acute exacerbation of COPD (ICD-9: 491.21, 491.22, 493.21, 493.22; ICD-10: J44.0, J44.1).

The outcome measure is whether a patient used the hospital (inpatient stay and emergency room visit) with a primary diagnosis of COPD (ICD-9: 491.21, 491.22, 491.8, 491.9, 492.8, 493.20, 493.21, 493.22, 496; ICD-10: J41.8, J42, J43.*, J44.*) in the subsequent year.

For asthma, we will use Schatz et al’s [20,82,83] method to find asthma patients. A patient is deemed to “have asthma if he/she has 1) ≥1 diagnosis code of asthma (ICD-9 493.*; ICD-10 J45/J46.*) or 2) ≥2 asthma-related medication dispensing records (excluding oral steroids) in a one-year period, including β-agonists (excluding oral terbutaline), inhaled steroids, other inhaled anti-inflammatory drugs, and oral leukotriene modifiers.” [84] The outcome measure is whether a patient used the hospital with a primary diagnosis of asthma (ICD-9 493.*; ICD-10 J45/J46.*) in the subsequent year.

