As mentioned in Aim 1, we will use temporal features to convert longitudinal data to tabular data, with 1 column per feature. Then we can apply our previous automatic explanation method [59]. Each patient is represented by the same set of features and is marked as either high risk for future hospital use or not. From historical data, our method mines association rules linked to high risk. An example rule is as follows: the ratio of inhaled steroid to beta agonist dispensing to the patient decreased over 12 months AND sulfur dioxide level was ≥3 parts per million for ≥5 days in the past week ⟶ high risk. The first item on the left-hand side of the rule is an actionable temporal risk factor. Two interventions for the first item are to (1) assess COPD controller medication compliance and change, prescribe, or raise the dose of the medication if needed and (2) assess the patient for COPD triggers and ensure the patient stays away from them. Our paper [71] listed several interventions for a few other temporal risk factors. By discussion and consensus, the clinical experts in our team will check the mined rules and drop those making little or no sense clinically. For every rule that remains, our clinical team will mark the actionable temporal risk factors in it and list zero or more interventions that address the reason shown by the rule.

At the time of prediction, for every patient our most accurate model projects to be at high risk for future hospital use, we will find and show all of the association rules whose left-hand side conditions the patient satisfies, and list the interventions linking to these rules as our suggestions. Each rule shows a reason why high risk is anticipated for the patient. Users of our automatic explanation function can give feedback to help us find and drop unreasonable rules [64].

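### ICD-9 493.20–493.22 count as both COPD and asthma while the ICD-10 lists share no code, so the adult-asthma label changes meaning across the data years

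*Protocol article*

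**What the plan says.** All the definitions stand in the protocol article's section on COPD and asthma cases and outcomes. It announces three test cases: "we will develop and test our approach using (1) COPD, (2) pediatric asthma, and (3) adult asthma".

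- **COPD outcome:** hospital use "with a primary diagnosis of COPD (ICD-9: 491.21, 491.22, 491.8, 491.9, 492.8, 493.20, 493.21, 493.22, 496; ICD-10: J41.8, J42, J43.*, J44.*) in the subsequent year". The same nine ICD-9 codes serve for case finding, with a minimum age of 40.
- **Asthma outcome:** "The outcome measure is whether a patient used the hospital with a primary diagnosis of asthma (ICD-9 493.*; ICD-10 J45/J46.*) in the subsequent year". The same codes serve for case finding.
- **Asthma by dispensing alone:** a patient also qualifies with "≥2 asthma-related medication dispensing records (excluding oral steroids) in a one-year period, including β-agonists (excluding oral terbutaline), inhaled steroids" and certain other drugs. No exclusion of patients who meet the COPD definition is stated.
- **COPD through respiratory failure:** this criterion requires a secondary code of "acute exacerbation of COPD (ICD-9: 491.21, 491.22, 493.21, 493.22; ICD-10: J44.0, J44.1".

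Under Aim 1, models are trained on the first 12 years of IH data and the best ones are tested on the 13th, with each outcome taken in the subsequent year. KPSC and UWM are handled similarly, and whatever is said of COPD applies to asthma in all five aims.

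**The concern.** A label used to train and test a classifier should mean the same thing in both sets of data. Here, a hospital use with primary code 493.22 in an ICD-9 year is an event for the COPD model and for the asthma model. The codes that the article groups with it under ICD-10 are an event for COPD only. Nothing about the patient has changed between the two; only the coding system has.

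The adult-asthma model may therefore learn some admissions as positives that the test year scores as negatives. Cross-validation inside the training years would estimate accuracy on a mixed label, and the held-out year would estimate it on a narrower one. A difference between the two would then combine true drift with a change of definition. The same label feeds the warning days of Aim 2, the simulated stays of Aim 3, the high-risk rules of Aim 4 and the sample of hospital users in Aim 5.

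**Working it through.** The article gives no figure of its own to reproduce on this point. The check compares the printed lists and then does arithmetic on the stated data years.

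**1. Overlap of the code lists**

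| List | COPD | Asthma | Shared |
|---|---|---|---|
| ICD-9 | 491.21, 491.22, 491.8, 491.9, 492.8, 493.20, 493.21, 493.22, 496 | 493.* | 493.20, 493.21, 493.22 (3 of 9) |
| ICD-10 | J41.8, J42, J43.*, J44.* | J45/J46.* | none |
| COPD exacerbation, ICD-9 | 491.21, 491.22, 493.21, 493.22 | 493.* | 493.21, 493.22 (2 of 4) |
| COPD exacerbation, ICD-10 | J44.0, J44.1 | J45/J46.* | none |

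The exacerbation rows are two code sets for one condition, not a one-to-one mapping. They are enough to show that the article regards 493.21 and 493.22 as COPD and places their ICD-10 counterparts outside asthma.

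**2. Where the change of meaning falls**

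Inputs from the Datasets section: IH 2005–2018, KPSC 2009–2018, UWM 2012–2018. Inputs from the accuracy evaluation in Aim 1: the last index year (2017) is the test year with outcomes in 2018, and earlier index years are for training. Calendar years are assumed, and the IH split is carried over to the other two sites.

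- IH: index years 2005–2016, outcome years 2006–2017, 12 years.
- KPSC: index years 2009–2016, outcome years 2010–2017, 8 years.
- UWM: index years 2012–2016, outcome years 2013–2017, 5 years.

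The date of the coding change is not in the article, so a range is used. For a change at the start of year T, the ICD-9 share of training-outcome years is (T − first outcome year) / number of outcome years.

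| Site | T = 2014 | T = 2016 | T = 2017 |
|---|---|---|---|
| IH | 8/12 = 67% | 10/12 = 83% | 11/12 = 92% |
| KPSC | 4/8 = 50% | 6/8 = 75% | 7/8 = 88% |
| UWM | 1/5 = 20% | 3/5 = 60% | 4/5 = 80% |

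For every T in this range, the 2018 test outcomes are entirely ICD-10. The share also differs between sites for one and the same T, so the article's cross-site comparison of asthma models would mix labels in different proportions.

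**3. The dispensing route**

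This route does not depend on the coding version. The example rule under Aim 4, where the discussion is about COPD, uses "the ratio of inhaled steroid to beta agonist dispensing to the patient decreased over 12 months", so the article itself expects COPD patients to receive drugs on the asthma list. COPD patients can therefore enter the adult-asthma cohort in any year. The stated prevalences give only a ceiling on their share of adult asthma cases:

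- IH: 4.1/8.6 = 48%
- KPSC: 4.1/10.8 = 38%
- UWM: 4.1/9 = 46%

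The floor is 0%. These ceilings assume that the prevalences were counted with the article's own case definitions, which it does not say.

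**4. What cannot be computed**

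The article gives no frequency of 493.2x, and the sign of the effect is open. A model trained with 493.2x as positive may rank such patients high and find them negative in 2018, which lowers AUC. COPD-only patients brought in by dispensing may instead be easy to rank as non-users, which raises it.

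**The case against.** The best case for the plan is that nothing in it requires the test cases to be disjoint. A patient can have both diseases and be eligible for both models, no hypothesis pools COPD with asthma, and the asthma definition is a quoted and cited case-finding method. All of this stands, so shared patients alone are no contradiction. Nor does the overlap of cases reach pediatric asthma or ages 18 to 39, because COPD requires age 40 or older. None of it explains why one kind of admission is asthma under one coding system and not under the next. The planned conversion to a common data model does not settle this either, because the outcome is stated in ICD codes.

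A reader might infer three stronger things that the article does not support.

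- **That the asthma definition contains the COPD case.** Six of the nine COPD ICD-9 codes lie outside 493.*. Tiotropium, the only drug named in the COPD criteria, is not named in the asthma drug list.
- **That easy negatives inflate AUC against the 0.1 target.** The target is a gain over a comparator retrained on the same data, so both models face the same cohort. As an illustration, suppose AUCs of 0.85 and 0.75 among asthma patients, 0.95 for both models against COPD-only non-users, and a share c of such non-users. The difference is then 0.1(1 − c), which is 0.088, 0.076 and 0.064 for c = 0.12, 0.24 and 0.36. On these assumed values the gain shrinks.
- **That the top-1% list is diluted.** Patients who are easily ranked as non-users would seldom enter that list.

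**Conclusion.** The point holds as an inconsistency of definition. ICD-9 493.20–493.22 belong to both diseases, for cases and for outcomes. The ICD-10 lists are disjoint, and the article's own grouping puts the counterpart of 493.21 and 493.22 under COPD only. The adult-asthma label therefore changes meaning within the data.

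That the change separates training from test data rests on an assumed coding change between the start of 2014 and the start of 2017. On that assumption, most IH training-outcome years (67% to 92%) have the ICD-9 meaning and the test outcomes have none of it. The consequence for AUC and for the top-1% hit rate is unknown in size and direction. One of the three test cases is chiefly affected. The correction is worth making before the analysis because it is cheap and the label is used in every aim.

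**What to change.** Give 493.2x one meaning in both coding systems: remove 493.20–493.22 from the asthma case and outcome codes and keep them under COPD, in line with the article's own grouping. Report the present 493.* definition as a sensitivity analysis.

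Because dispensing can bring COPD patients aged 40 or older into the adult-asthma cohort in any year, also report the adult-asthma results without patients who meet the COPD definition. This should be a sensitivity analysis and not a primary exclusion. As an exclusion it would drop patients who have both diseases and change the target population, and it is not needed to repair the coding inconsistency.

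The cost is a change to the code list and the cohort query, plus two further runs, with no new data; the article says that analysis had not begun. There would be slightly fewer adult-asthma cases and events and slightly less comparability with the cited method. Patients under 40 whose only qualifying record is a 493.2x code would fall into neither test case, as already happens to those with only a J44 code under ICD-10.

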#### Temporal Feature Extraction

We will use a new method to semiautomatically extract predictive and clinically meaningful temporal features from longitudinal data. These features will be used to build the final predictive model and to automatically identify actionable temporal risk factors for each patient at high risk for future hospital use. Our new method is semiautomatic, as its final step involves a human to extract features through visualization [71]. It generalizes to many clinical applications and is sketched as follows, with more details described in our design paper [71].

Our method uses LSTM [35], a type of deep neural network that models long-range dependencies and often reaches higher prediction accuracy than other algorithms [40]. A lot of work has been performed using LSTM to construct predictive models on medical data [36-39,85]. LSTM performs computations on a sequence of input vectors from the same patient, one vector after another. Every input vector is marked by a time step *t*. After finishing the whole sequence, LSTM gains results that are combined with static attributes such as gender [86] to predict the outcome of the patient. Every input vector contains information of one patient visit such as vital signs and diagnoses. The sequence length can differ across patients. This helps increase model accuracy, because LSTM can use as much of each patient’s information as possible, without dropping information to make every patient have the same length of history. In addition, this enables us to make timely predictions on new patients without waiting until every patient acquires history of a certain length. With information from only one visit, LSTM can start making projections on the patient.

As Figure 1 shows, an LSTM network includes a sequence of units, one for each time step. In the figure, each unit is denoted by a rounded rectangle. ⨂ represents the element-wise multiplication. ⨁ represents the element-wise sum. A unit contains an input gate *i_t_*, a hidden state *h_t_*, an output gate *o_t_*, a forget gate *f_t_*, and a memory cell *c_t_*. The memory cell maintains long-term memory and keeps summary information from all of the previous inputs. Every element of the memory cell vector represents some learned temporal feature. As shown by Karpathy et al [87], only approximately 10% of the memory cell vector elements could be interpreted [88]. This is because LSTM puts no limit on the number of input vector elements that can connect to every memory cell vector element. All of the input vector elements could be adopted in every element of the input and forget gates’ activation vectors and connect to every memory cell vector element. Consequently, no limit is put on the number of attributes utilized in every learned temporal feature.

It is difficult to understand a feature that involves many attributes. To address this issue, we will use multi-component LSTM (MCLSTM), a new type of LSTM that can automatically drop uninformative attributes. As Figure 2 shows, an MCLSTM has several component LSTM networks, each using some rather than all of the longitudinal attributes. By limiting the number of attributes connecting to every memory cell vector element, more memory cell vector elements will depict clinically meaningful and more generalizable temporal features. As LSTM often produces more accurate models than other algorithms [36-39], the learned features tend to be predictive. As patient attributes are collected at a different frequency from air quality and weather attributes, we specify certain component networks for the former and the others for the latter. To let data tell which component network uses which attributes, we use a new exclusive group Lasso (least absolute shrinkage and selection operator) regularization method. It combines exclusive Lasso [89,90] and group Lasso [91] to reach 2 goals jointly. First, in each component network, every attribute competes with every other attribute. When one is employed, the others are less likely to be employed. Second, in each component network, all of the input vector weight matrix elements connecting to the same attribute tend to become nonzero (or zero) concurrently. Nonzero means the attribute is employed. We will use TensorFlow [62] to train MCLSTM and use our previous method [84,92] to automate hyperparameter value selection.

Kale et al [93-97] showed that in a deep neural network, we can use training instances that incur the highest activations of a neuron to find clinically meaningful features. After training the MCLSTM network, we proceed as follows to identify zero or more such features from every memory cell vector element at the final time step of the network. First, we find several training instances that incur the highest activations in the memory cell vector element. Second, in each of those training instances, we find one or more segments of the input vector sequence termed effective segments, each tending to represent a useful temporal feature. Third, we partition all spotted effective segments into multiple clusters and visualize each cluster separately to identify zero or more clinically meaningful temporal features. As shown in Wang et al [98], such a visualization could help us find and address data quality issues such as an implausible order of events, boosting model accuracy. For each identified feature, [name] and a clinician in our team will jointly arrive at an exact mathematical definition of an extracted feature. Many extracted features capture trends more precisely than the raw features learned by LSTM. This also boosts model accuracy.

**Figure 1 figure1:**
[figure not shown]
A long short-term memory network.

**Figure 2 figure2:**
[figure not shown]
A multi-component long short-term memory network having K components.

#### Aim 1’s Final Predictive Models

We will use the extracted temporal features to convert longitudinal data to tabular data, with 1 column per feature, and add static features. Health care system features such as the number of a physician’s patients of a given race can boost model accuracy [64,65,99] and are included as static features. We will employ Weka [61] to construct Aim 1’s final predictive models. As shown in Aim 4, these models are suitable for automatic explanation. We will use supervised algorithms and our previous method [84,92] to automatically select the algorithm, feature selection technique, imbalanced class handling method, and hyper-parameter values among all of the applicable ones. We will do manual fine-tuning if needed.

Using historical data up to the prediction time point, we will build 3 sets of models, one for each of 3 combinations: COPD at IH, KPSC, and UWM. For each of IH, KPSC, and UWM, the corresponding set of COPD models will be built for all of the COPD patients in that health care system. Unlike integrated health care systems IH and KPSC, UWM has most of its patients referred from other health care systems and has fairly incomplete data on many of its patients. To reduce incomplete data’s impact on model accuracy, we will use our previous constraint-based method [100] to find patients tending to receive most of their care at UWM and build models on and apply models to them. Previously, we showed that a good constraint for all types of UWM patients on average is that the patient lives within 5 miles of a UWM hospital and has a UWM primary care physician [100]. Yet, the optimal distance threshold could vary across various types of patients because of their different characteristics. Intuitively, a UWM COPD patient is likely to keep using and get a large portion of his/her care from UWM, even if the patient lives at some distance away from the closest UWM hospital. In comparison, a patient who visited a UWM emergency room once owing to a car accident may no longer use UWM after that visit. We will use the approach in our previous work [100] to find an optimal distance threshold for COPD patients. As noted earlier, we will develop and test our techniques on asthma as well.

#### Accuracy Evaluation and Justification of the Sample Size

The discussion below is for IH data. The cases with KPSC and UWM data are similar. As we need to compute outcomes for the subsequent year, we essentially possess 13 years of IH data over the past 14 years. We will train and test models in a usual way. We will do a stratified 10-fold cross-validation [61] on the data in the first 12 years to train models and to estimate their accuracy. The data in the 13th year will be employed to gauge the performance of the best models, mirroring future use in clinical practice. We will select the best model using the standard performance metric AUC [61]. A care management program typically enrolls 1% to 3% of COPD patients [32]. Of the upper 1% of COPD patients the model projects to be at the highest risk of using the hospital, we will report the percentage of patients using the hospital in the subsequent year. For a program taking 1% of COPD patients based on the model’s prediction results, this percentage reflects the degree of correct enrollment. To find the variables vital for high accuracy, we will conduct backward elimination [74] to remove features on the condition that accuracy does not drop >0.02. We will compare the variables vital for high accuracy on IH data with those on KPSC and UWM data. Using the variables available in both the IH and KPSC/UWM datasets, we will build the best predictive model on IH data and compare the model’s accuracy on IH data with that on KPSC/UWM data.

We will test the hypothesis that using our techniques can boost model accuracy. To do this, we will use a 2-sided Z test to compare the AUCs of 2 predictive models built in a way like that in Obuchowski [101]. The first predictive model will use the best machine learning algorithm and take all features essential for high accuracy. The second model will be adapted from those in the literature. For each predictive model for hospital usage reported in the literature [19-28], we will retrain it on our dataset using the attributes appearing in both the original model and our dataset. The most accurate one of the retrained models will be the second model. Our hypothesis is as follows:

Null hypothesis: The first model reaches the same AUC as the second.Alternative hypothesis: The first model reaches a higher AUC than the second.

The categorical outcome variable of hospital usage has 2 possible values (classes). To the best of our knowledge, every predictive model for hospital usage reported in the literature reaches an AUC <0.8 [19-28]. “Using a two-sided Z-test at a significance level of 0.05 and assuming for both classes a correlation coefficient of 0.6 between the two models’ prediction results, a sample size of 137 instances per class has 90% power to detect a difference of 0.1 in AUC between the two models,” [65] like an increase of AUC from 0.8 to 0.9. The IH data in the 13th year include around 35,000 COPD patients, offering enough power to test our hypothesis. This conclusion remains valid if the actual correlation coefficient differs somewhat from the assumed one.

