Current models for predicting the health outcomes and health care costs of individual COPD and asthma patients have low prediction accuracy for several reasons:

Many temporal features with high predictive power are either frequently unused in an existing model or yet to be found. Google recently applied long short-term memory (LSTM) [35], one kind of a deep neural network, to all the attributes in the electronic health record to automatically learn temporal features from longitudinal data [36]. For forecasting each of the 3 outcomes: long hospital stay, unanticipated readmissions within 30 days, and in-hospital mortality, this increased the AUC by approximately 10% [36]. Multiple other studies [37-39] showed similar results for a variety of clinical prediction tasks. This aligns with what has taken place in areas such as video classification, natural language processing, and speech recognition, where temporal features that LSTM automatically learned from data outperform those mined from data by other methods or specified by experts [40,41].Although >40 risk factors for undesirable outcomes in COPD/asthma have been identified [19,20,23,28,42-48], an existing model usually uses only a few (eg, <10) [19-24,26-28]. Existing models were often constructed based on data obtained from clinical trials or old fashioned electronic health records collecting limited variables [49]. No published model adopts all of the known risk factors available in modern electronic health records collecting extensive variables [49].Environmental information such as air quality and weather variables are known to impact COPD and asthma outcomes [43,50-52], but with rare exceptions [25], are infrequently used in existing models.

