### Aim 1: Use Temporal Features to Provide Accurate Early Warnings of Poor Outcomes and Assess the Impact on Prediction Accuracy.

We will semiautomatically extract predictive and clinically meaningful temporal features from patient, air quality, and weather data, and build models to predict a patient’s health outcome. Each feature involves one or more raw variables. The number of possible features is almost infinite. In addition, factors such as environmental variables beyond air quality and weather can influence patient outcomes. This study does not intend to exhaust all of the possible features and factors that can influence patient outcomes and achieve the highest possible prediction accuracy in theory. Rather, our purpose is to show that using temporal features can improve risk warning timeliness, prediction accuracy, and care management. A nontrivial boost in health outcomes can greatly benefit society. As is adequate for our target decision support application and typical with predictive modeling, our study focuses on associations.

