### Aim 2: Assess Using Temporal Features’ Impact on Risk Warning Timeliness

The discussion below is for IH data. The cases with KPSC and UWM data and with asthma are similar.

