### Aim 3: Assess Using Temporal Features’ Potential Impact on Outcomes Via Simulations

To assess the value of a predictive model for future clinical deployment, we need to appraise care management outcomes if the model is adopted and decide how to generalize the predictive model to other sites gathering differing sets of variables. Our predictive models will be constructed on IH, KPSC, and UWM data. Our simulations will guide how to employ the predictive models in other health care systems. No previous study has decided the variables most crucial for COPD and asthma model generalization. We will apply our simulation method to care management of (1) COPD patients, (2) asthmatic children, and (3) asthmatic adults.

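### Aims 1 to 3 are framed as the effect of temporal features, but their tests compare the whole set of techniques with a literature model and cannot attribute a gain to temporal features

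*Protocol article*

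**What the plan says.** **Purpose and titles.** The introduction to Aim 1 states that "our purpose is to show that using temporal features can improve risk warning timeliness, prediction accuracy, and care management". Aim 2 is titled "Assess Using Temporal Features’ Impact on Risk Warning Timeliness" and Aim 3 "Assess Using Temporal Features’ Potential Impact on Outcomes Via Simulations".

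**First model.** In the section Accuracy Evaluation and Justification of the Sample Size (Aim 1): "The first predictive model will use the best machine learning algorithm and take all features essential for high accuracy". Its candidate inputs include air quality and weather variables (Data Preprocessing), and health care system features and the extracted temporal features (Aim 1's Final Predictive Models). The pipeline will "automatically select the algorithm, feature selection technique, imbalanced class handling method, and hyper-parameter values among all of the applicable ones".

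**Second model.** "The second model will be adapted from those in the literature". Each published model is retrained on the attributes found both in it and in the dataset, and the most accurate retrained model is taken.

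**Tests.** The Aim 1 hypothesis is worded for the techniques as a whole: "We will test the hypothesis that using our techniques can boost model accuracy". The outcome evaluation sections of Aims 2 and 3 use the same two models and the same kind of wording.

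**What literature models contain.** Under Gap 2, "an existing model usually uses only a few (eg, <10"), against more than 40 known risk factors. Environmental data are described as infrequently used, with rare exceptions, and under Gap 1 temporal features as seldom used.

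**The concern.** The question the study sets itself is whether temporal features add something. The contrast it tests changes several things at once: temporal features, the number of other variables, usually the environmental data, and possibly the algorithm. A higher AUC, more warning days or fewer simulated inpatient stays would show that the package works, but not which part of it works.

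This matters because temporal feature extraction is the novel and laborious part of the project: it needs a new network type, visualisation of clusters, and a clinician to help define each feature. A health care system deciding whether to adopt that step needs to know what it adds beyond a richer set of ordinary variables.

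**Working it through.** No figure in the plan states the share of the gain due to temporal features, so the main check is a comparison of texts. Three short calculations follow.

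**1. What differs between the two models**

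| Component | First model | Second model | Status of the difference |
|---|---|---|---|
| Extracted temporal features | Candidate inputs | Seldom used in the literature | Expected |
| Number of variables | All those essential for accuracy | Usually fewer than 10 | Expected |
| Air quality and weather | Candidate inputs | Infrequent, with rare exceptions | Expected, not certain |
| Health care system features | Added as static features | Only if in the published model | Expected |
| Algorithm and tuning | Searched automatically | Not stated for the retraining | Possible |

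The Gap 2 section lists unused temporal features, few risk factors and little environmental data as separate reasons for low accuracy. The section on Aim 1's final models adds that health care system features can improve accuracy. So the document itself names non-temporal sources of gain that the contrast does not hold fixed.

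**2. Whether anything else in the plan isolates temporal features**

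- Backward elimination (Aim 1) drops features as long as accuracy does not fall by more than 0.02. It protects no class of features, so the first model could keep few temporal features or none and still beat the second.
- The Aim 3 sensitivity analysis evaluates variable combinations grouped by likely co-availability at other sites. It gives estimates without a test and is not arranged as with against without temporal features.

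**3. Illustration that the planned test can be positive with no temporal effect**

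All inputs are assumptions: 35,000 patients for training and 35,000 for testing; event rate about 5%; logistic model with intercept -3.6 and independent standard normal predictors; 5 literature variables (coefficient 0.4 each), 15 further static variables (0.22 each), 4 environmental variables (0.2 each) and 10 temporal features (0 each); paired DeLong Z test; 40 runs.

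| Contrast | Mean AUC difference | Runs significantly favouring the fuller model |
|---|---|---|
| Full model against literature variables (0.807 against 0.721) | 0.086 | 40 of 40 |
| Full model against same model without temporal features | -0.0005 | 0 of 40 |

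The size of 0.086 follows from the chosen coefficients. Only the possibility is shown, not its likelihood.

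**4. Whether an added contrast would have useful power in Aim 1**

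The plan gives 137 instances per class for 90% power at an AUC difference of 0.1. The Aim 2 section gives about 2,000 COPD patients at Intermountain Healthcare (IH) who used the hospital in the 14th year, which is the outcome year for the 13th-year data. With the variance and correlation behind the plan's figure unchanged, the detectable difference scales with the square root of sample size:

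0.1 × √(137/2000) = 0.1 × √0.0685 = 0.1 × 0.262 ≈ 0.026.

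**5. The same for Aim 2**

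Reproducing the plan: with exponential times, n patients per model and a one-sided 0.05 F test with 2n and 2n degrees of freedom, the detectable rise is 180 × (F₀.₉₅ × F₀.₈₀ - 1). For n = 600 this is 27.8 days, as stated (power 0.800). For n = 2,000 it is 14.7 days; a check by 180 × (exp(2.4865 × √(2/2000)) - 1) also gives 14.7. This uses the plan's own distributional assumptions, which treat the two sets of times as independent.

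**The case against.** **The tests match their hypotheses.** The hypotheses speak of the techniques as a bundle, and the most accurate retrained literature model is a legitimate and fairly demanding benchmark for that question. This stands. A reader might infer that the tests are invalid, or that the study can show nothing of value. The document does not support that: the gap lies between the tests and the purpose and titles, and rewording could close it.

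**The comparator may be richer than it looks.** A reader might infer that the second model certainly lacks environmental data, has fewer than 10 variables, contains no temporal feature and gets no algorithm search. The text does not say so. The comparator pool (references 19 to 28) includes the exception cited for environmental data (reference 25), and that study is not among those cited for the small number of variables. Temporal features are called seldom used, not never used. Whether retraining searches algorithms is not stated. This stands too, so the differences are expected rather than certain. It does not restore attribution, because even a richer literature model would not match the first model in everything but temporal features.

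**Partial handling exists.** Backward elimination would show whether temporal features survive, and the Aim 3 table bears on what variables contribute. Both are useful description, but neither isolates the temporal contribution.

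**The illustration is built to give its result.** This is true: temporal effects were set to zero and other effects were not. It carries no information on how large the misattribution would be in these data.

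**Conclusion.** The point holds in a limited form. The tests in Aims 1 to 3 can establish that the combined techniques do better than the best retrained literature model. They cannot attribute any part of that gain to temporal features, which is what the declared purpose and the aim titles promise.

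The temporal share cannot be computed from the document and could lie anywhere from none to nearly all of the gain. The conclusion needs only that the two models are not matched on the non-temporal components, which the planned construction does not ensure. It does not need the literature model to be poor in every respect. Nor does it assume that the authors will credit temporal features wrongly in their reports; the document gives no basis for predicting that.

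This should be changed before analysis, but it does not undermine the literature comparison.

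**What to change.** Keep the literature comparison as planned and add a nested comparator for Aims 1 to 3. It should use the same algorithm search, the same training years and the same static, environmental and health care system variables, but without the temporal features extracted through the long short-term memory network.

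Define its inputs with care. The introduction treats any variable formed by transforming longitudinal attributes as a temporal feature, so a yearly count would qualify. There are two consistent choices:

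- enter longitudinal attributes only as most recent values, and call the contrast with against without temporal features; or
- allow conventional summaries such as counts, and label the contrast extracted temporal features against conventional summaries.

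Base any statement about temporal features on this contrast, and report how many of them remain in the first model after backward elimination. If the comparator is not added, restate the purpose and the titles of Aims 1 to 3 as the effect of the combined techniques.

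**Cost.** Further model fits for each site and disease, and repeated runs of the Aim 2 warning-day calculation and the Aim 3 simulations. The expected difference will be smaller than the goals of 0.1 in AUC and 30 days, which should stay attached to the literature comparison. The added contrast needs its own planning assumptions. At IH, differences of about 0.026 in AUC (90% power) and 14.7 days (80% power) would be within reach on the plan's own assumptions. The Aim 3 assumption of 5% against 1% would also need review for this contrast.
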